### Interventions

Participants from both groups will perform the supervised training program three times per week for 12 weeks, with at least 24 h of interval between intervention sessions. No instruction for home exercise will be given. Participants will be instructed to maintain their physical and sports activities.

The duration of each session for the STG will be around 60 min and for the SPTG around 75 min. All sessions will be supervised by an experienced physiotherapist (> 5 years). The description of the exercises has been made simple and clear; therefore, physiotherapists will need minimal training to apply the exercises (Additional file 1 – supplementary material).

The STG and SPTG programs will be based on the training principles recommended by the American College of Sport Medicine (ACSM) [32]. The exercises were chosen based on a study that successfully applied the protocol to people with PFP [30] and other strength training studies [22, 42–45].

To perform the exercises, ankle weights, free weights and/or dumbbells, and elastic bands will be used. The load to be used in the exercises of both groups will be determined based on the 10RM (repetition maximum) test to estimate the 1RM—the 10RM load indicates approximately 75% of the 1RM load [46]. As the participants have PFP, the 1RM test could exacerbate the symptoms. For exercises using an elastic band, the 1RM test will be performed. The 1RM will be considered the highest elastic band (considering the color of the elastic), in which the participant can perform a single repetition [22].

Regarding pain management during exercise, a level equal to or lower than three points in VAS will be accepted, and if any participant presents pain above this level, the exercise will be modified according to the variations that are also in the exercise protocol (Additional file 1). In addition to pain management, the presence of muscle failure will also be monitored. Exercise will be interrupted if muscle failure occurs, which will be considered as the participant's inability to move a specific load beyond a critical joint angle [47] or as the inability to complete a repetition in the stipulated range of motion due to fatigue [48].

As an adherence strategy to encourage participants attending training sessions, both groups will receive face-to-face education sessions about possible causes and consequences of PFP, pain management, importance of physical activity for the treatment, and other questions that may arise during the intervention period. In addition, telephone calls will be made to remind participants about the sessions. The intention is that the participants feel part of the treatment, understand how the intervention can help them, and, thus, attend the intervention sessions [49].

### Strength Training Group (STG)

The strength training program will consist of applying resistance and progressive exercises for strength gain. Initially, the goal will be to develop neuromotor control and endurance (load < 50% 1RM), and in subsequent weeks, the goal will be to develop muscle strength (load > 70% 1RM) (Fig. 2). The protocol will initially focus on hip and trunk muscles, and after 4 weeks of training, knee muscle exercises (weight-bearing or non-weightbearing) will be included.

**Fig. 2 Fig2:**
[figure not shown]
Strength Training Group (STG) schedule

At each training session, at least five exercises (out of a total of 15 exercises) will be chosen and applied by the therapist. From these five exercises, one will be for hip extensors, one for hip abductors, one for knee extensors, and two for the trunk. Additional file 1 provides a complete description of all exercises that may be applied to participants. According to the evolution of the participants, regarding pain and ease of execution, the therapist will perform the progression of the loads and even the substitution of one exercise for a more complex one as long as it is one of the program exercises.

### Power and Strength Training Group (PSTG)

Participants assigned to this group will perform the same exercise program as the STG and power training exercises (fourth column of Additional file 1). Initially, the focus will be on neuromotor control and resistance development (load < 50% 1RM). Afterwards, the goal will be to develop strength (load> 70% 1RM) and muscle power (load between 40 and 60% 1RM) (Fig. 3).

**Fig. 3 Fig3:**
[figure not shown]
Power and Strength Training Group (PSTG) schedule

### Outcome measures

Primary outcomes will be pain intensity and physical function, and secondary outcomes will be kinesiophobia, self-reported improvement, quality of life, peak hip and knee torque, and hip and knee rate of force development. The primary outcomes will be evaluated at baseline, and after 6 weeks, 12 weeks, 3 months, 6 months, and 1 year. The secondary outcomes will be evaluated at baseline and immediately after the interventions.

### Pain intensity

Pain intensity will be measured using the Numeric Rating Scale (NRS-11), where 0 represents “no pain” and 10 represents “the worst pain possible.” Participants will indicate their usual pain and worst pain during the past week [40].

### Physical function

The Anterior Knee Pain Scale (AKPS), translated and validated into Portuguese [50], will be used to assess subjective symptoms such as anterior knee pain and functional limitations related to PFP. The items evaluated in the questionnaire are patellar subluxation, limp, pain, walking, climbing stairs, and sitting for a long time with bent knees. It has a score from 0 to 100 points, where 100 means no pain and/or functional limitations and 0 means constant pain and various functional limitations [51]. The AKPS is a reliable and valid instrument for assessing function in individuals with PFP [40].

### Kinesiophobia

The evaluation of kinesiophobia will be performed by the translated and validated Portuguese version of the Tampa Scale for the Kinesiophobia questionnaire [52], which consists of 17 items that assess fear of movement, injury or recurrence of injury [53]. This questionnaire is a four-point Likert scale, where the sum of the answers can vary from 17 to 68, and scores higher than 37 indicate the presence of kinesiophobia [54].

### Quality of Life

Participants will be assessed using the specific subscale for quality-of-life assessment of Knee Injury and Osteoarthritis Outcome Score (KOOS). This subscale comprises four questions and each one will be scored from 0 to 4, where 0 represents extreme knee problems and 4 that there are no knee problems. The sum of these questions will be used for further analysis [55, 56].

### Muscle capacity

Isometric torque and RFD of knee extensors, hip extensors, and abductors will be evaluated using an isokinetic dynamometer (Biodex Multi Joint System 3, Biodex Medical Systems Inc., New York, USA), with a sampling frequency of 100 Hz.
Knee extensors: the participants will be placed in a sitting position with hips at 85° of flexion and neutral position for transversal and frontal planes, and the knee of the assessed limb at 60° of flexion [13]. The resistance pad will be fixed with a velcro strip just above the lateral malleolus and the rotation axis of the dynamometer will be aligned with the lateral femoral epicondyle.Hip extensors: the participants will be in a prone position on the testing table of the dynamometer and their legs will be off the table. The assessed lower limb will be placed with the hip at 30° of flexion, and the participants should keep the knee at 90° of flexion and avoid hip rotations during the test. The resistance pad will be fixed with a velcro strip just above the popliteal fossa, and the rotation axis of the dynamometer will be aligned with the center of the hip joint in the sagittal plane near the greater trochanter of the femur [12, 57].Hip abductors: the participants will be placed in a side-lying position, whereby the top leg will be the assessed side. The assessed hip will be in neutral position for all three planes, the knee will also be in neutral position, and the participants will be instructed to keep their toes pointed forward and not to bend their knee during the test [58]. The resistance pad will be fixed with a velcro strip 5 cm above the upper edge of the patella and the rotation axis of the dynamometer will be aligned to a point representing the intersection of two lines: one line directed inferiorly from the posterior superior iliac spine towards the knee, and the other line oriented medially and posteriorly to the greater trochanter of the femur toward the midline of the body.

For the whole assessment, the participants should perform the contraction as powerfully and as quickly as possible and maintain the contraction for 5 s. For each assessed muscle group, three maximal contractions will be collected with a 1-min interval between them. The participants will be verbally encouraged to achieve maximum power throughout all the contractions. Previously to the data collection, the participants will be familiarized with the tests by performing two submaximal contractions and one maximal contraction. A 3-min interval will be adopted between familiarization and data collection. Isometric torque measures will be normalized by body mass (Nm/kg × 100), and the highest value of the three repetitions will be used for statistical analysis for each muscle group [12].

A test-retest reliability study will be conducted to verify intra-examiner reliability of measurements by evaluating 10 participants in two moments, with an interval of 3 to 7 days.

To calculate the RFD, the highest value of the three repetitions for each muscle group will be used [12]. The normalized torque data will be exported and processed in the Matlab Software (Mathworks, Natick, Massachusetts, USA, version 2008b). RFD will be calculated using the slope of the torque/time curve. The slope will be obtained by dividing the variation of the normalized torque (Nm/Kg X 100, represented as %) by the time variation (ms) from the start of the contraction until 30% and 90% of the maximal isometric torque [59, 60]. The beginning of the contraction will be defined as the moment when the isometric torque exceeds 2% of the peak torque [61]. Thus, higher RFD values indicate an increased ability to generate force rapidly [62].

### Self-reported improvement

The self-reported improvement with reference to the start of the study will be quantified using the Global Rating of Change (GROC). This tool is a 15-point Likert-type scale that measures a patient's perception of a change in knee pain following a specific treatment [63]. The scale ranges from − 7 (a very great deal worse) to + 7 (a very great deal better), with 0 (zero) indicating no change. Changes of 4 points or more on this scale have been previously considered as clinically important in patients with knee pain [64].

### Blinding

The researcher in charge of the evaluations and the data processing will be blinded to the group allocation. The participants and the therapist will not be blinded to the group allocation due to the differences between our interventions which are easily detectable.

### Minimizing missing data

In order to avoid and minimize missing data, as an adherence strategy to encourage participants to attend training sessions, both groups will receive face-to-face education sessions about possible causes and consequences of PFP, pain management, importance of physical activity for the treatment, and other questions that may arise during the intervention period. In addition, telephone contacts will be made to remind participants about the sessions and the evaluations. Regarding the 3 month-, 6 month-, and 1-year follow-ups, the researcher will contact the participant by telephone and send them the online questionnaire.

### Data management

Data are being collected at the Laboratory of Evaluation and Intervention in Orthopedics and Traumatology (LAIOT) at the Federal University of São Carlos (UFSCar). Data will be stored at the Physical Therapy Department at UFSCar with a password-protected computer file, to which only researchers will have access. The main researcher will have a backup copy of all the information.

The study results will be released in conferences, such as scientific conferences, internationally and nationally, and through articles published in peer-reviewed journals. This research is a part of a PhD thesis, and the publishing rights are owned by the authors. The results will be frequently presented to the supervising professor ([name]).

### Data monitoring

Researchers will monitor participants throughout the study development (assessment and interventions). The supervising professor ([name]), who will be blind to the group allocations, will monitor any adverse effects and perform database management and statistical analyses.

Adverse events during the study procedures, either during assessments, interventions, or follow-up, will be registered and reported. Adverse events will be considered any symptom or disease that is related or not to the evaluations and the intervention.

The University Graduate Program will supervise the integrity of the data, and the responsible Internal Data Monitoring Committee will have access to the patient allocation, while the whole analysis will be confidential. The supervising professor ([name]) will ensure that the University Graduate Program and Internal Data Monitoring Committee will be provided with access to source data/documents, ensuring the confidentiality of the participants.

### Harm

Participant data will be carefully accessed, and all harm and complications of the treatment will be reported together with the other results of this trial, if any.

### Auditing

The University Graduate Program will supervise the integrity of the data. Moreover, the results will be frequently presented to the supervising professor ([name]), who will be blind to the group allocations, and will verify if data are accurate, complete, and verifiable and that the conduct of the study complies with the currently approved protocol.

### Statistical analysis

The intention-to-treat approach will be applied for all analyses [65]. The differences from baseline will be used in the analysis. The effects of intervention on the outcome measures will be assessed by analysis of variance (ANOVA). For pain and physical function (primary outcomes), a 2-by-6 analysis of variance will be used with the groups (STG and PSTG) as the independent factor and time (baseline, 6-week, post intervention, 3-month follow-up, 6-month follow-up, and 12-month follow-up) as the repeated factor. For kinesiophobia (secondary outcome), a 2-by-3 analysis of variance (2 groups and 3 time points) will be used. For quality of life and muscle capacity (hip and knee torque; hip and knee RFD) (secondary outcomes), a 2-by-2 analysis of variance (2 groups and 2 time points) will be used. For GROC outcome (secondary outcomes), the reference criterion of treatment success will be a score of + 6 (much improved) or higher and these data will be presented as a percentage. Moreover, chi-square tests will be performed to compare the percentage of patients who perceived much improvement in each group based on the GROC scale. Separate models will be used for each outcome measure. For significant group-by-time interactions, planned pairwise comparisons with post hoc Bonferroni will be used to determine differences. The mean difference and 95% CI will be also calculated for each comparison. In cases of missing data, the multiple imputation method will be adopted to impute missing values [66], and per-protocol analysis will be also performed. The significance level will be 0.05. All the statistical analysis will be performed using a Statistical Package for the Social Sciences software program (version 20.0, SPSS, Inc., Chicago, IL, USA), and the researcher who will perform the analysis will be blinded to the group allocation. Interim analyses will not be performed. No additional analyses will be performed in the trial.

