### Sample size

The sample size of this study was calculated considering a statistical power of 80%, alpha of 5%, and an estimated 15% of sample losses. In order to detect a 2-point difference in pain NRS [40] with a standard deviation of 2.8 points [41], a sample size calculation indicated 37 participants in each group.

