### Randomization and allocation

All participants who give consent for participation and who fulfill the inclusion criteria will be randomized to the Strength Training Group (STG) or to the Power and Strength Training Group (PSTG) with a 1:1 allocation ratio. Randomization will be performed using consecutively numbered, sealed and opaque envelopes previously prepared and randomly assigned by a random number generator program (www.randomization.com). Allocation concealment will be ensured, since the randomization code will only be released after the participant has been included in the clinical trial. A researcher not involved in the assessment process will perform the randomization and participant allocation to the groups by opening the envelopes after the baseline evaluation. The physiotherapist, responsible for the intervention, will open the envelope and, will find the treatment condition to be conducted in this participant. The researcher responsible for assessments is not allowed to receive information about the group allocation. Thus, randomization will be conducted without any influence of the physiotherapists and researchers responsible for assessments and interventions.

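### The stated 80% power belongs to one uncorrected two-group comparison; the planned interaction gate followed by Bonferroni is a different procedure and generally delivers less

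*Protocol article*

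**What the plan says.** Sample size section: "The sample size of this study was calculated considering a statistical power of 80%, alpha of 5%, and an estimated 15% of sample losses". The target is set as follows: "In order to detect a 2-point difference in pain NRS", with a standard deviation of 2.8, and "a sample size calculation indicated 37 participants in each group". The section mentions no repeated measures, interaction test or multiplicity.

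Statistical analysis section: each primary outcome (pain and physical function) goes into a 2-by-6 ANOVA with group and time as factors. Baseline is listed as one of the six time levels, although the same section also says that changes from baseline are analysed. Group comparisons then follow this rule: "For significant group-by-time interactions, planned pairwise comparisons with post hoc Bonferroni will be used to determine differences". A separate sentence provides a mean difference and 95% CI for each comparison, and the section ends by ruling out additional analyses. The Bonferroni family size is not stated. Neither this section nor Outcome measures names a single primary time point.

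**The concern.** The two sections describe different tests. The sample size assumes that the groups are compared once, at 5%. The analysis compares them only if a 5-degree-of-freedom interaction test is significant, and then at a reduced level. A group difference has to pass both steps to be declared, so the power of the whole procedure cannot exceed that of either step. The trial could therefore miss the 2-point benefit for which it was sized more often than the one time in five that the protocol implies. If the estimates are tied to the same rule, a non-significant interaction may also leave the reader without a clear between-group result.

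**Working it through.** **1. The plan's own figure.** Inputs from the Sample size section: difference 2, SD 2.8, 80% power, alpha 5% (two-sided assumed, as sidedness is not stated), 15% losses. Allocation is "with a 1:1 allocation ratio".

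n = 2 × (1.96 + 0.8416)² × (2.8/2)² = 30.8, so 31 evaluable per group; 31/0.85 = 36.5, so 37. This matches the article. The basis is one uncorrected two-sample comparison.

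**2. Bonferroni alone, without the gate** (normal approximation). With 31 per group, the expected z is 2 / (2.8 × √(2/31)) = 2.81.

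- One comparison: Φ(2.81 − 1.96) = 80%.
- Five visits (0.05/5 = 0.01, critical value 2.576): Φ(2.81 − 2.576) = 59%.
- Six visits: 57%.

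If all 37 per group are analysed, these become 87%, 69% and 67%. To keep 80% at one visit with a family of five, n = 2 × (2.576 + 0.8416)² × 1.4² = 45.8, so 46 evaluable; 46/0.85 = 54.1, so 55 per group.

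**3. Gate and comparison together** (simulation). From the article: 2 groups, 6 time levels, SD 2.8 and the 2-point difference. Derived: 31 per arm. Assumed: the difference is 2 points at all five post-baseline visits; a Greenhouse-Geisser correction; SD 2.8 is the SD of raw scores; within-person correlation of 0.3, 0.5 or 0.7, either equal between all visits or decaying with time. Results are in percent, with simulation error of up to a few points.

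| Result | Equal 0.3 / 0.5 / 0.7 | Decaying 0.3 / 0.5 / 0.7 |
|---|---|---|
| Interaction significant | 62 / 80 / 96 | 46 / 53 / 65 |
| And raw 12-week comparison at 0.05 | 51 / 64 / 75 | 39 / 43 / 54 |
| And raw 12-week comparison at 0.01 | 37 / 48 / 54 | 30 / 31 / 40 |
| And 12-week change score at 0.01 | 35 / 54 / 83 | 25 / 32 / 49 |
| No gate, one baseline-adjusted 12-week contrast at 0.05 | 82 / 89 / 97 | 79 / 81 / 88 |

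The article does not say whether 2.8 is the SD of raw scores or of changes. If it is the SD of changes, gate plus Bonferroni over five visits on change scores gives about 55 / 54 / 53% under equal correlation.

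**4. Shape of the effect.** In the six-level model, a fading effect (0, 1, 2, 1.5, 1, 0.5 points over the six levels) passes the gate less often than a sustained one: 49 / 63 / 89% against 62 / 80 / 96% under equal correlation.

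**5. Five-level variant.** If only the five post-baseline changes are modelled, a sustained effect is constant over time. The interaction then rejects at its null rate of about 5%. The group main effect in that model has power of about 85 / 96 / 99% (equal) and 74 / 79 / 85% (decaying).

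**The case against.** The size of the loss depends on things that the article does not fix, and some choices remove it.

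- **Family size.** With two groups there is one between-group comparison per visit, so a Bonferroni family of one is possible. The gate still applies: the uncorrected row stays at 39–75% with 31 per arm. With all 37 analysed and equal correlation 0.7, it reaches 82–85%.
- **Success at any visit.** No single primary time point is named, so success might mean significance at any visit. After the gate, with Bonferroni over five visits, a sustained effect then succeeds in about 61 / 72 / 79% (equal correlation, 31 per arm), and a fading one in 35–57%. With high correlation or no losses, sustained or building effects reach up to 88% on raw scores and 97% on change scores.
- **Change scores.** With SD 2.8 as the raw-score SD and equal correlation 0.7, gate plus Bonferroni over five visits reaches 79–83%.

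These exceptions stand, so a reader who infers that 80% is never reached goes too far.

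A reader might also infer that a sustained benefit leaves the interaction null, so that the comparison is never made. That needs the five-level model, which contradicts the six levels listed. Even there the effect would show in the group main effect, for which the article states no decision rule. Nor is a sustained effect the easiest to miss: in the six-level model a fading one is missed more often.

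Finally, a reader might infer that a non-significant interaction leaves no between-group estimate at all. The sentence on mean differences and CIs is separate and carries no condition of its own. It follows the gated sentence without clearly lifting the gate, so it is ambiguous rather than a proven gap.

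**Conclusion.** The point holds as a mismatch between sample size and analysis. The 80% is the power of one uncorrected two-group comparison, which is not the procedure planned, and under that procedure it is generally not met.

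The firmest part needs no correlation assumption: if Bonferroni covers five visits, power at any one visit falls from 80% to about 59%, and the gate can only lower it further. The rest depends on the stated assumptions. The gate passes in about 46–96% of trials, and the full procedure at 12 weeks succeeds in about 39–75% uncorrected or 30–54% with Bonferroni over five visits, on raw scores. Correlation, effect profile, family size and type of SD are not given, so these are ranges and not predictions for this trial.

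**What to change.** Remove the interaction gate. Estimate the between-group difference in each primary outcome from a baseline-adjusted repeated-measures model, and report the mean difference and 95% CI at every visit whatever the interaction p-value. This also settles whether baseline is a time level or a covariate.

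Name in advance the pain contrast to which the 80% power applies, for example the end of the 12-week intervention. Keep physical function and the follow-up visits in their stated roles, and write down the multiplicity rule that covers them. If the gate and Bonferroni are kept instead, state the family size and restate the power for that procedure.

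The cost is wording. No further participants are needed for the ungated 12-week contrast, which has 79–97% power in the scenarios above. The Trial status section reports that no analysis has been performed, so the change can still be made before results are seen. The real downside is that one visit must take priority for pain. The long-term comparisons, which the Introduction and Discussion emphasise, then carry less confirmatory weight.
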